## Abstract

**Background:**

The optimal management of patients with resectable gastric cancer continues to evolve in Western countries. Following publication of the US Intergroup 0116 and UK Medical Research Council MAGIC trials, there are now two standards of care for adjuvant therapy in resectable gastric cancer, at least in the Western world: postoperative chemoradiotherapy and perioperative epirubicin/cisplatin/fluorouracil (ECF) chemotherapy.

We hypothesize that adding chemoradiation to standard perioperative ECF chemotherapy will achieve further survival gains. We also believe there are advantages to administering chemoradiation in the preoperative rather than postoperative setting. In this article, we describe the *TOPGEAR* trial, which is a randomised phase III trial comparing control arm therapy of perioperative ECF chemotherapy with experimental arm therapy of preoperative chemoradiation plus perioperative ECF chemotherapy.

**Methods/Design:**

Eligible patients with resectable adenocarcinoma of the stomach or gastroesophageal junction will be randomized to receive either perioperative chemotherapy alone (3 preoperative and 3 postoperative cycles of ECF) or perioperative chemotherapy plus preoperative chemoradiation. In the chemoradiation arm, patients receive 2 cycles of ECF plus chemoradiation prior to surgery, and then following surgery 3 further cycles of ECF are given.

The trial is being conducted in two Parts; Part 1 (phase II component) has recruited 120 patients with the aim of assessing feasibility, safety and preliminary efficacy of preoperative chemoradiation. Part 2 (phase III component) will recruit a further 632 patients to provide a total sample size of 752 patients. The primary endpoint of the phase III trial is overall survival. The trial includes quality of life and biological substudies, as well as a health economic evaluation. In addition, the trial incorporates a rigorous quality assurance program that includes real time central review of radiotherapy plans and central review of surgical technique.

**Discussion:**

*TOPGEAR* is an international, intergroup collaboration led by the Australasian Gastro-Intestinal Trials Group (AGITG), in collaboration with the Trans-Tasman Radiation Oncology Group (TROG), European Organisation for Research and Treatment of Cancer (EORTC) and the NCIC Clinical Trials Group. It addresses a globally significant question that will help inform future international standards for clinical practice in resectable gastric cancer.

**Trial registration:**

Australian New Zealand Clinical Trials Registry: ACTRN12609000035224. Registered 30 May 2009

## Background

The optimal management of patients with resectable gastric cancer continues to evolve in Western countries. Following publication of the US Intergroup trial 0116 in 2001, postoperative chemoradiation became a standard of care for patients who had undergone potentially curative surgery [1]. This trial randomly assigned 556 patients following surgery to either observation or adjuvant therapy with 4 monthly cycles of bolus 5-fluorouracil (5-FU) and leucovorin combined with 45 Gy of radiotherapy. With a median follow-up of 5 years, the 3-year survival rate was 50 % in the chemoradiation group versus 41 % in the surgery alone group (p = 0.005). Although adjuvant chemoradiotherapy has been adopted as standard of care in North America and some parts of the world, it is still uncommonly used in other countries. This relates mainly to criticism of INT0116 with regard to surgical quality as 54 % of patients underwent less than a D1 lymph node dissection despite the recommendation for a D2 dissection. There are also concerns amongst medical and radiation oncologists regarding the outdated chemoradiation regimen that was employed.

The UK Medical Research Council MAGIC trial that was published in 2006 provides an alternative standard of care for adjuvant therapy in resectable gastric cancer [2]. This trial randomly assigned 503 patients with resectable gastric cancer to either perioperative chemotherapy and surgery or surgery alone. Chemotherapy consisted of 3 preoperative and 3 postoperative cycles of epirubicin, cisplatin and 5-FU (ECF). With a median follow-up of 4 years, the 5-year survival rate was 36 % in the perioperative chemotherapy group versus 23 % in the surgery alone group (hazard ratio 0.75; p = 0.009). A significantly greater proportion of patients in the perioperative chemotherapy group underwent curative R0 resection (79 % vs 70 %), and resected tumors were significantly smaller and less advanced in this group. Of those patients who started chemotherapy, 90.7 % completed preoperative chemotherapy. However, of those who completed preoperative chemotherapy and surgery, only 49.5 % also completed postoperative chemotherapy.

Since the publication of the INT0116 and MAGIC studies, clinicians and patients have been faced with the dilemma of which adjuvant or neoadjuvant strategy to employ. By analysing failure patterns, each approach appears to improve survival through different mechanisms. The perioperative chemotherapy approach using ECF reduces systemic failure, while postoperative chemoradiation improves locoregional control. Since both strategies provide moderate gains in survival, we hypothesize that adding chemoradiation to standard perioperative ECF chemotherapy will achieve even greater survival gains in a similar patient population. Furthermore, we believe there are advantages to testing the addition of chemoradiation by administering it in the preoperative rather than postoperative setting. One of the main advantages of preoperative therapy is the potential for tumor downstaging with an increase in the complete R0 resection rate. Preoperative therapy is also much better tolerated than postoperative therapy, thereby ensuring that all patients receive the intended treatment. Both of these advantages were clearly demonstrated in the MAGIC study. The strategy of preoperative chemoradiation for gastric cancer has thus far only been tested in a small number of phase II studies, which have demonstrated safety, tolerability and high rates of pathological complete response [3, 4].

In this article, we describe the study protocol of a currently accruing trial, which has the acronym *TOPGEAR* (Trial Of Preoperative therapy for Gastric and Esophagogastric junction AdenocaRcinoma). *TOPGEAR* is a randomised phase III trial, which compares control arm therapy of perioperative ECF chemotherapy with experimental arm therapy of preoperative chemoradiation plus perioperative ECF chemotherapy. The design of this trial allows a comparison of the MAGIC regimen with an INT0116 regimen, but with the specific intent of bringing the chemoradiation approach into the preoperative setting. This trial is an international, intergroup collaboration led by the Australasian Gastro-Intestinal Trials Group (AGITG), in collaboration with the Trans-Tasman Radiation Oncology Group (TROG), European Organisation for Research and Treatment of Cancer (EORTC) and the NCIC Clinical Trials Group.

## Methods/design

### Design

*TOPGEAR* is a two arm randomised phase II/III trial in which patients are randomised to either perioperative chemotherapy alone (3 preoperative and 3 postoperative cycles of ECF) or perioperative chemotherapy plus preoperative chemoradiation (Fig. 1). In the chemoradiation arm, patients receive 2 cycles of ECF plus chemoradiation prior to surgery, and then following surgery 3 further cycles of ECF are given. The method of randomisation will be using minimisation where patients will be stratified on age, primary tumor site, clinical tumor stage, nodal status, treating institution, and staging investigations. The protocol has been approved by the Clinical Research Ethics Committee of the Cancer Institute NSW, as well as individual institutional ethics committees. All patients have given written informed consent before participating in the trial.

**Fig. 1 Fig1:**
[figure not shown]
Trial schema. Patients are randomised to either perioperative chemotherapy alone or perioperative chemotherapy plus preoperative chemoradiation (preop CRT). X = capecitabine

The primary objective of this phase III trial is to investigate whether perioperative chemotherapy plus preoperative chemoradiation improves overall survival compared to perioperative chemotherapy alone. The trial will be conducted in two Parts using an adaptive phase II → III design. Part 1 (phase II component) has recruited 120 patients with the aim of assessing feasibility, safety and preliminary efficacy of preoperative chemoradiation. The endpoints for Part 1 are pathological complete response (pCR) rate, toxicity, treatment compliance and accrual. If based on an interim analysis of the first 120 patients, the experimental chemoradiation arm is shown to be safe and feasible, accrual is deemed to be satisfactory, and there is not clear evidence of lack of efficacy as reviewed by the Independent Data and Safety Monitoring Committee (IDSMC), recruitment will continue in the second Part of the study (phase III component), which will recruit a further 632 patients for a total of 752 (recruitment to Part 2 will begin prior to this interim analysis in a seamless transition). The primary endpoint of Part 2 will be overall survival, with progression-free survival, toxicity, and pathological response rate as secondary endpoints.

### Participants

Eligible patients are those who meet all of the following eligibility criteria:Histologically proven adenocarcinoma of the stomach or gastroesophageal junction that is:Stage IB (T1N1 only, T2N0 not eligible) – IIIC, i.e. T3 – T4 and/or N + ve, according to AJCC 7th edition.Considered operable following initial staging investigations (surgeon believes that an R0 resection can be achieved).(Gastroesophageal tumors are defined as tumors that arise in the cardia or at the gastroesophageal junction that do not involve more than 2 cm of the lower esophagus, i.e. Siewert Type II and Siewert Type III)Age 18 years or olderEastern Cooperative Oncology Group (ECOG) performance status 0–1Adequate organ function defined as follows:Bone marrow: Hemoglobin ≥ 90 g/L, Absolute neutrophil count (ANC) ≥ 1.5 x 10^9^ /L, White blood cell count ≥ 3 x 10^9^ /L, Platelet count ≥ 100 x 10^9^ /LHepatic: Serum bilirubin ≤ 1.5 x ULN, AST and/or ALT ≤ 3.0 x ULNRenal: Serum creatinine ≤ 0.150 mmol/L, and calculated creatinine clearance ≥ 50 mL/minAny patient with a history of ischaemic heart disease and abnormal ECG, or who is over 60 years of age should have a pre-treatment evaluation of cardiac function with a MUGA scan or echocardiogram. Patients will only be included if the left ventricular ejection fraction is ≥ 50 %.

### Study treatments

#### Pre- and post-operative chemotherapy

ECF consisting of:Epirubicin 50 mg/m^2^ IV day 1Cisplatin 60 mg/m^2^ IV day 15-FU 200 mg/m^2^/day IV via 21 day continuous infusion. According to centre specific preferences, capecitabine 625 mg/m^2^ bid days 1–21 may be substituted for 5-FU. This regimen is named “ECX”. For simplicity, the text will refer only to ECF.

#### Chemoradiotherapy

Radiation therapy consisting of 45 Gy in 25 fractions, 5 days per week for 5 weeks + continuous infusional 5-FU 200 mg/m^2^/day, 7 days per week throughout the entire period of radiotherapy (or capecitabine 825 mg/m^2^ bid, days 1 to 5 each week of RT). Radiation therapy will be delivered to the entire stomach, any perigastric tumor extension, and regional lymph nodes according to detailed guidelines contained in the protocol.

#### Surgery

Surgical guidelines have been developed by the Surgical Subcommittee comprising surgeons from Australia, Europe and Canada in accordance with international standards. The acceptable resections include a total gastrectomy, a subtotal distal gastrectomy or an esophago-gastrectomy (for gastroesophageal junction tumors). The recommended operation is a D2 gastrectomy where possible, with a minimum approach being a D1+ gastrectomy aiming for complete resection of the primary cancer and its draining nodes.

The full trial protocol includes considerably more detail about chemotherapy concurrent medications and dose attenuations, radiation specifics (including contouring atlas) and surgery details.

### Quality assurance

The trial includes a comprehensive quality assurance program to ensure patient safety, appropriate trial conduct and data quality, including:

#### Surgical quality assurance

There is central review of surgical technique to ensure compliance with protocol guidelines. Each surgeon completes a trial operation form indicating the extent of surgery, the lymph node stations resected and the reconstruction. The form is reviewed by a Surgical Subcommittee, which will make an independent assessment of the extent of lymphadenectomy. In addition, the pathology will be reviewed and used as a surrogate for adequacy of resection. It is expected that at least 15 lymph nodes will be resected during a radical gastrectomy for cancer. Additionally, the Maruyama Index (MI) [5] will be assessed for each specimen. A low MI suggests an adequate lymphadenectomy and is associated with increased survival when compared with a high MI; this provides a second objective measure assessing surgical quality assurance in each group. Because of the importance of pathological assessment, the trial also incorporates a process of central pathology review.

#### Radiation therapy quality assurance (RTQA)

Because of the complexity of gastric irradiation, a comprehensive RTQA program has been developed to monitor protocol violations. The technical review will be conducted at 2 time points; pre-radiation therapy and post-treatment. The pre-treatment review will be conducted in “real time” - at least 1 week before radiation therapy is to begin, to allow any adjustments to be made. Approval of the treatment plan must be obtained prior to the patient starting radiotherapy. The main parameters to be evaluated will be clinical target volume (CTV) coverage and dose to organs at risk (OAR). An analysis of INT0116 demonstrated that 35 % of treatment plans contained protocol violations at initial pre-treatment review. The post-treatment review will assess compliance of radiotherapy delivery with protocol guidelines after completion of radiotherapy. The RTQA process will include the first 5 patients from each treatment centre; once an acceptable quality level is achieved, sites will be audited with one in every three patients.

### Substudies

#### Biological substudy

In addition to addressing clinical questions, the trial also incorporates a comprehensive biological research program. Blood, serum, plasma and tumor specimens will be biobanked. Tumor specimens will include material from pre-treatment biopsies and gastric resections. In addition to formalin-fixed / paraffin-embedded (FFPE) material, fresh frozen tissue (FFT) collection will be undertaken at a subset of Australian and Canadian centres. This will provide the potential for discovery using FFT specimens and validation with FFPE specimens. Broad objectives of the translational research program are to create a tissue bank of well curated biospecimens with coded clinical annotations and to undertake both discovery/hypothesis-generation and validation of existing hypotheses addressing the questions; “Are there genetic determinants of chemotherapeutic and radiotherapeutic response in gastric cancer?”, and “Are there biological differences in remnant disease after preoperative chemoradiation that differ from the primary (treatment naïve) lesion that could be used to target specific therapeutics?” In addition, the program will investigate a number of specific biomarkers identified *a priori*, which focus on both discovery/hypothesis generation and validation objectives.

#### Quality of life (QoL) and economic evaluation

This study will collect and assess QoL data for a large group of patients receiving different adjuvant treatments. QoL in this study will be assessed using the EORTC QLQ-C30 core questionnaire as well as the QLQ-OG25 module, which has been developed to measure QoL in patients with cancer of the esophagus, the gastroesophageal junction and the stomach. We hypothesize that perioperative chemotherapy plus preoperative chemoradiation will improve disease control and overall survival but may also be associated with greater treatment-related morbidity. Thus, related to the patient’s experience, a preference-based health status will also be collected for a subset of patients. The Health Utilities Index Mark3 (HUI3) will be used as an indirect measure of health preference; the HUI3 is a health-related QoL instrument and will be used to help estimate quality-adjusted life years (QALYs) for each intervention. A health economic assessment will be undertaken utilising information on QoL related to initial treatment, progression, overall survival and initial resource usage including treatment delivery as inputs.

### Statistical considerations

The sample size of the randomised phase III trial has been planned to ensure sufficient power to demonstrate an overall survival advantage of perioperative chemotherapy plus preoperative chemoradiation as compared with perioperative chemotherapy alone. The expected 5-year survival for perioperative chemotherapy alone is approximately 40 % and is supported by the observations from the MAGIC trial (5-year survival 36 %) [2]. We would consider an approximate 25 % relative increase in this rate (hazard ratio [HR] = 0.76) to be clinically worthwhile and feasible; this translates to an estimated 5-year survival of 50 %. The potential to achieve this incremental benefit is suggested by 3 pieces of information: i) the HR observed in the INT0116 trial with postoperative CRT was 0.74 [1]; ii) the odds ratio [OR] for 5-year survival observed in a meta-analysis of 3 trials comparing postoperative chemoradiation to surgery +/− chemotherapy was 0.45 [6]; and, iii) the OR for 5-year survival observed in a meta-analysis of 4 trials comparing preoperative radiation therapy to surgery alone was 0.62 [6, 7]. The objective of this randomised phase III trial is to determine whether these benefits of radiation therapy, especially when given in its most optimal form and timing of preoperative chemoradiation, translate into the same magnitude of benefit when patients receive perioperative chemotherapy. With 80 % power and 95 % confidence, 410 deaths need to be observed. We determine that this event number would be observed by accruing 720 patients over 5 years with an additional follow-up of 3 years. Allowing for a dropout rate of 7 %, accrual of 752 patients is required.

The differences in overall survival between the two treatment arms will be compared using an unadjusted two sided log-rank test at the p = 0.05 significance level (α = 0.05). Kaplan-Meier curves will be displayed. Survival will be characterized in terms of the median, and the probability of being alive at 6 months and at 12 months (based on Kaplan-Meier estimates). Ranges, 95 % confidence intervals on the treatment estimates, and the hazard ratio (estimated by Cox proportional hazards regression) will also be computed. Exploratory multivariable modelling will be performed adjusting for baseline levels of primary tumor site, age, gender nodal status and clinical tumor stage. The analyses will be performed on an intention to treat basis.

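### The primary survival test ignores the factors used in minimisation; stratifying it by a few of them would be a cheap, modest gain in power

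*Protocol article*

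**What the plan says.** The Design section of the protocol article allocates by minimisation and lists six factors: "patients will be stratified on age, primary tumor site, clinical tumor stage, nodal status, treating institution, and staging investigations". Under Statistical considerations, overall survival in the two arms "will be compared using an unadjusted two sided log-rank test", at a two-sided 0.05 level, with the hazard ratio from Cox regression. Adjustment appears only as exploratory multivariable modelling, "adjusting for baseline levels of primary tumor site, age, gender nodal status and clinical tumor stage". That list covers four of the six allocation factors, adds gender, and leaves out institution and staging investigations. The word unadjusted is written into the primary test, so this is a stated choice and not a detail left to an analysis plan that is not shown.

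**The concern.** Minimisation removes most of the chance imbalance between arms in the factors it uses. An unadjusted log-rank test computes its variance as if that imbalance could still occur. If the factors predict survival, the test statistic then varies less than its nominal variance says. The test rejects slightly too seldom under the null, the confidence interval is slightly too wide, and the same deaths yield less power than an analysis that reflects the allocation. At stake is efficiency in a trial planned at 80% power, where more power would otherwise have to come from more deaths.

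**Working it through.** **Inputs from Statistical considerations.** "two sided log-rank test at the p = 0.05 significance level"; "With 80 % power and 95 % confidence, 410 deaths need to be observed"; "hazard ratio [HR] = 0.76"; control arm: "The expected 5-year survival for perioperative chemotherapy alone is approximately 40" per cent; experimental arm: "this translates to an estimated 5-year survival of 50" per cent. The allocation ratio is not stated, so 1:1 is assumed.

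**1. The plan's own figure.** Under proportional hazards, 40% against 50% gives HR = ln 0.5 / ln 0.4 = 0.7565.
- Schoenfeld, d = 4(1.960 + 0.842)² / (ln HR)²: 417 deaths at HR 0.76 and 404 at 0.7565.
- Freedman, d = (1.960 + 0.842)² × [(1 + HR)/(1 − HR)]²: 423 and 409.
- Power at 410 deaths, Φ(√410 × |ln HR| / 2 − 1.960): 79.4% at HR 0.76 and 80.7% at 0.7565.

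The stated 410 deaths are reproduced.

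**2. Simulation assumptions.** 752 patients; biased-coin minimisation (probability 0.8) on five binary factors plus 60 institutions; analysis at 410 deaths; 4,000 runs per scenario, and 10,000 more for two null scenarios. The Monte Carlo standard error at 4,000 runs is about 0.6 points for power and 0.3 for type I error. The article gives no prognostic strengths, so three sets were assumed, with a standard deviation of the prognostic log hazard of 0.25 (weak), 0.44 (moderate: T stage HR 1.6, nodal status HR 1.8) and 0.68 (strong: 2.2 and 2.5).

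**3. Conservatism under the null.** Model standard error of the unadjusted log HR against its true standard deviation:
- Moderate: 0.0989 against 0.0956, ratio 1.03. Implied size 2[1 − Φ(1.960 × 1.03)] ≈ 4.3%; simulated 4.3 to 4.7%.
- Strong: 0.0989 against 0.0907, ratio 1.09. Implied size ≈ 3.3%; simulated 3.4 to 3.5%.
- No or weak prognosis: simulated about 4.5%, within about two Monte Carlo standard errors of 5%.

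The stratified log-rank test (strata T and N) had simulated size 4.6 to 5.4% across all scenarios. A Cox model adjusted for the five binary factors had 5.3 to 5.6% in the moderate and strong cases.

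**4. Power at 410 deaths, unadjusted / stratified.**

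| Assumed prognosis | 40% vs 50% as the overall effect | Gain | HR 0.76 as the within-stratum effect | Gain |
|---|---|---|---|---|
| Weak | 80.2 / 80.6% | 0.4 | 78.4 / 79.2% | 0.8 |
| Moderate | 81.7 / 84.3% | 2.6 | 74.8 / 77.8% | 3.0 |
| Strong | 83.3 / 88.9% | 5.6 | 67.3 / 75.5% | 8.2 |

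**5. Eligibility.** The Participants section requires T3–T4 and/or node-positive disease, so no patient is low-risk on both T and N. The runs above do not impose this. Excluding that cell makes T and N negatively related and narrows the spread of risk. Two further simulations imposed it:
- With 40% against 50% as the overall effect, the unadjusted test has about 81 to 84% power. The stratified gain is about 1.5 points (moderate) or 3 to 3.5 points (strong), and unadjusted type I error is about 5% and 4%.
- With 0.7565 as the within-stratum HR (75 centres, 3,000 runs, assumed T/N prevalences of 50/50% and 70/60%; prognostic HRs for T, N, site and age of 1.6, 1.8, 1.3, 1.2 or 2.0, 2.5, 1.4, 1.3), the restriction cut the prognostic variance by 35 to 48%. The gain was 0.7 to 2.4 points (moderate) and 4.0 to 4.5 (strong), against 2.6 to 3.7 and 6.6 to 7.6 without it.

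**The case against.** The strongest reply is that the planned test is conventional and valid, and delivers the power it promises. That stands. The article states its effect as overall survival at five years, 40% against 50%, and on that reading the unadjusted test keeps 80% or more in every scenario. Figures in the 60s or 70s arise only when the planned HR is taken as the effect within strata, which makes the overall difference smaller than the plan's.

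The unadjusted HR does lie nearer 1 than the adjusted one (0.755 against 0.743 in the moderate case). A reader might call this bias. It is non-collapsibility: the two are different estimands, and the unadjusted one matches the Kaplan-Meier curves and the sample-size basis.

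The mismatch between the exploratory covariates and the allocation factors carries little weight. The list already contains T stage, nodal status and site, institution is too sparse to use by centre, and adding gender does no harm.

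It is also fair to say that changing the primary test of an accruing trial is more than a wording change, and that the adjusted Cox test slightly over-rejected in simulation. The first calls for a documented amendment; the second favours the stratified log-rank test. Neither removes the gain at equal deaths.

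**Conclusion.** The point holds as a modest efficiency improvement. The gain from stratifying at the same 410 deaths runs from near zero (weak prognosis), through about 1 to 3 points (moderate), to about 3 to 8 points (strong), and sits at the lower ends once eligibility is respected. All of this rests on assumed prognostic strengths, prevalences and minimisation settings. The direction is not in dispute if the factors are prognostic.

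A reader might infer that the trial is underpowered, or that its false-positive rate is wrong in a harmful direction. The article supports neither. The stated 80% is kept for the overall effect it specifies, and any departure from 5% is conservative, clearly visible only under strong assumed prognosis. What is forgone is extra power that the plan never claimed.

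**What to change.** Before any unblinded survival analysis, amend the plan so that the primary test is a two-sided 0.05 log-rank test stratified by clinical T stage, nodal status and tumour site, with the HR from a Cox model stratified the same way. Keep the unadjusted log-rank test, the unadjusted HR and the Kaplan-Meier curves as the supportive analysis. Do not stratify by individual centre: 752 patients over approximately 75 centres is about 10 each.

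The article does not give the factor levels. If each of the three has two, eligibility leaves 3 T/N combinations × 2 sites = 6 strata, or 410 / 6 ≈ 68 deaths per stratum on average, which is ample.

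The cost is a documented amendment. The stratification factors are already recorded for allocation, and no extra patients, deaths or follow-up are needed. The Discussion reports 170 patients recruited, so there is time to prespecify it. The small downside is that the primary HR becomes conditional on the strata, so the unadjusted HR should be reported beside it.
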